### Outcome measures

#### Primary outcomes

**Disability** The Roland-Morris (RM) questionnaire is one of the most widely used measures to assess disability in patients with low back pain [36]. This questionnaire was designed to evaluate low back pain, with 24 statements that describe different daily activities that can be affected by low back pain. The participant has to select the statements that describe the limitations produced by their low back pain. The Spanish version of the RM has shown good psychometric properties (reliability and validity) [37].

**Pain** IMMPACT recommends the use of NRS as a core outcome measure of efficacy in clinical trials of chronic pain treatments [38]. The scale is composed of 11 numbers ranging from 0 to 10, with 0 meaning ‘No pain’ and ‘10’ meaning ‘Pain as bad as you can imagine’. Two different scales will be used, one to assess low back pain and the other to examine sciatica pain.

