**Methods:**

A randomised controlled trial with 180 CLBP patients recruited from specialised care will be conducted. Participants will be randomly assigned to three conditions: Control group (CG), CBT, and CBT supported by ICTs (CBT + ICT). Participants belonging to the three conditions will receive a conventional rehabilitation program (back school). The CBT group program will last six sessions. The CBT + ICT group will use the internet and SMS to practice the therapeutic strategies between sessions and in the follow-ups at their homes. Primary outcome variables will be self-reported disability and pain intensity. Assessment will be carried out by blinded assessors in five moments: pre-treatment, post-treatment and 3-, 6-, and 12-month follow-ups. The influence of catastrophizing, fear-avoidance beliefs, anxiety and depression in response to treatment in the primary outcomes will also be analysed.

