### Randomization

Participants will be randomly assigned to one of three conditions (Control, CBT and CBT +ICT). Participants will be stratified according to their level of disability: severe (Roland Morris Disability Questionnaire (RMDQ) score > 15), moderate (RMDQ score between 8 and 14) and mild (RMDQ score <7). Allocation will be performed by a computer-generated list according to the degree of disability at baseline. It will be supervised by a statistician not belonging to the research group and unaware of the study characteristics.

During recruitment, the allocation sequence will be concealed. Due to the nature of the interventions, it is not possible to blind the participants. The physiotherapists administering the sessions and the assessors will be unaware of the participants’ allocation. Data analysis will be conducted without being aware of the intervention received by the participants.

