### Sample size

The study has been designed taking into consideration changes of 2 points in the pain intensity measured by the numerical rating scale (NRS) and of 3 points in the RMDS. These changes have been recognised as clinically relevant [35]. According to the results of a previous CLBP sample treated in our health centre, the mean disability according to the RMDS presented a standard deviation of 4, while the mean pain intensity displayed a standard deviation of 2. Considering these data and an alpha of 0.01 and a beta of 0.9 for two-tailed mean tests, the required sample size is 53 to detect changes in disability and 30 to detect changes in pain intensity. Considering an attrition of 15%, the sample will need 60 participants per condition. For further analysis of treatment response according to high or low catastrophizing, fear-avoidance beliefs, depression and anxiety, disability measured by the RMDS will be considered with an alpha of 0.05 and beta of 0.8, resulting in a sample size of 28 participants per group.

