Intra-group changes in the continuous variables along the time points will be explored with Student’s T-test for paired samples. To assess if there are differences among the groups according to pain, disability and the rest of the variables, we will use analysis of covariance (ANCOVA) for each dependent variable. In all the tests, the independent variable will be the group, while the covariate variable will be the basal level of each dependent variable. It will be necessary to have comparable levels of both types of variables to understand correctly the ANCOVA results. Therefore, we will perform different Student’s T test estimations, one for each dependent variable, considering each group as an independent variable in each case. To evaluate whether the changes in the three groups have happened in a different way, we will estimate different ANOVA, an analysis for each dependent variable. In all cases, the independent variable will be the group and time in which the data are collected. In this analysis, we will also study possible interactions. Furthermore, we will evaluate the correlations between the variables using Rho-Pearson and Spearman according to normality. We will also use two multiple linear regression models for pain and disability as dependent variables and in both models, gender, age, pain, catastrophizing, fear avoidance, days taken off at work and time evolution will be employed as independent variables.

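### The trial is sized on one pain outcome at alpha 0.01, but two unranked pain scales are primary and no deciding test, contrast or test level is named, so family-wise error is not fixed

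*Protocol article*

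**What the plan says.** - **Arms.** Under Randomization: "Participants will be randomly assigned to one of three conditions (Control, CBT and CBT +ICT"). No contrast between arms is named as primary.
- **Primary outcomes.** The abstract gives two: "Primary outcome variables will be self-reported disability and pain intensity". The Primary outcomes section adds, for pain: "Two different scales will be used, one to assess low back pain and the other to examine sciatica pain". It does not say which scale is the primary one.
- **Sample size.** The targets are "changes of 2 points in the pain intensity measured by the numerical rating scale (NRS) and of 3 points in the RMDS". On variability, "the mean disability according to the RMDS presented a standard deviation of 4, while the mean pain intensity displayed a standard deviation of 2". The error rates are "an alpha of 0.01 and a beta of 0.9 for two-tailed mean tests"; the second figure must be power. This gives 53 per arm for disability and 30 for pain, and 60 per arm after allowing for 15% attrition. A separate calculation for treatment-response subgroups uses alpha 0.05.
- **Analysis.** Under Collection and data analysis, continuous variables are compared between groups by t-test or Mann-Whitney, depending on a Kolmogorov test. For group differences, "we will use analysis of covariance (ANCOVA) for each dependent variable", with the baseline value as covariate. For differing change over time, "we will estimate different ANOVA, an analysis for each dependent variable". The primary time point is 12 months and intention-to-treat comes first. No significance level for tests appears in this section. A 95% interval is mentioned once, for descriptive statistics.

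**The concern.** The sections do not fit together. The sample size has one pain outcome and the outcome section has two, so the reader cannot tell which scale the 30 per arm refers to or which one decides the pain result. Three between-group approaches are applied to the same outcomes and can disagree. The level that justifies the sample size is not carried into the analysis.

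The trial asks two efficacy questions: whether CBT adds to back school, and whether ICT adds to CBT. Without a named contrast, test and level, neither has a protected answer, and a positive claim could rest on whichever scale and analysis happened to favour it.

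**Working it through.** **1. The plan's own figures.** Inputs from Sample size: RMDQ difference 3, SD 4; NRS difference 2, SD 2; two-sided alpha 0.01; power 0.90. Formula: n per arm = 2 × [SD × (z₀.₉₉₅ + z₀.₉₀) / difference]², with 2.576 + 1.282 = 3.857 and 3.857² = 14.88.
- RMDQ: 2 × (16/9) × 14.88 = 52.9, so 53.
- NRS: 2 × 1 × 14.88 = 29.8, so 30.

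Both reproduce, so the design does rest on 0.01 and on one pain outcome.

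**2. Counting comparisons.** Three arms give three pairs. With two primary scales there are 2 × 3 = 6 comparisons; with three scales, 3 × 3 = 9.

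**3. Simple limits.** For m independent tests the chance of any false positive is 1 − (1 − α)^m, and the Bonferroni bound is m × α.

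| m | α | Independent | Bound |
|---|---|---|---|
| 6 | 0.01 | 5.85% | 6% |
| 9 | 0.01 | 8.65% | 9% |
| 6 | 0.05 | 26.5% | 30% |
| 9 | 0.05 | 37.0% | 45% |

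**4. Simulation with correlated scales.** No true effects, 51 per arm (60 × 0.85), all three pairs tested without a gate, 10,000 trials per setting. Assumptions not in the article: correlation between scales 0.3 to 0.7; baseline-to-follow-up correlation 0.5; the group-by-time ANOVA represented by a t-test on change scores.

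| α | Primary scales | ANCOVA only | Any of ANCOVA, t-test, change score |
|---|---|---|---|
| 0.01 | 2 | 4.8–5.2% | 9.6–10.5% |
| 0.01 | 3 | 6.2–7.4% | 12.4–14.8% |
| 0.05 | 2 | 19.9–22.6% | 33.8–38.6% |
| 0.05 | 3 | 25.4–31.0% | 42.8–50.8% |

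A separate simulation with pairwise z-tests gave 4.8–5.2% and 6.3–7.6% for the two 0.01 rows with one test. Hence about 5 to 8% overall at 0.01.

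**5. Power at the planned level.** With 51 completers per arm the RMDQ statistic has expected value 3 / (4 × √(2/51)) = 3.787. Power is Φ(3.787 − 2.576) = Φ(1.211) = 88.7%, slightly below 90% because 51 is fewer than 53.

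**The case against.** The strongest reply is that the article is tighter than this suggests.

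- **The level.** 0.01 is the only level stated for the primary outcomes, and it stands beside a different level, 0.05, for subgroups, so it looks deliberate. Articles often do not repeat the design alpha, and a multiplicity rule may sit in an analysis plan that is not shown. A reader might infer from the 95% interval that tests will be run at 0.05. The article does not support this, because that interval belongs to descriptive statistics.
- **The number of tests.** A reader might count nine ungated pairwise comparisons under each of three tests. The ANCOVA and ANOVA, however, use group as a three-level factor and read as omnibus tests; only the two-sample tests imply pairs. With one omnibus test per scale, simulation under the same range of scale correlations gives 8–10% (two scales) or 11–14% (three) at 0.05, and about 2–3% at 0.01.
- **The role of each test.** ANCOVA is introduced as the assessment of group differences, the ANOVA as a check on differing change, and the further t-tests read as comparability checks for the ANCOVA. The 12-month time point is fixed, which limits selection across visits.
- **The sciatica scale.** A reader might suspect that many patients would score near zero on it. The article gives no figure for this, and it excludes neurologic deficit, not radiating pain.

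These points lower the size of the problem. They do not remove it. The outcome section still conflicts with the abstract and sample size over how many pain outcomes there are. No analysis is called primary, and an omnibus test alone does not say whether ICT adds to CBT. The concern is with what the article states inconsistently, not with detail left to another document.

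**Conclusion.** The point holds in a limited form. The article leaves the primary pain scale, the deciding test, the contrasts and the applicable level open or inconsistent, so the family-wise error of the primary analysis is not fixed. With pairwise testing it is about 5 to 8% if 0.01 and one test per comparison apply. If 0.05 were used, it is 20 to 31% with one test, or 34 to 51% if any of three tests may be used. These ranges rest on the assumed correlations, on ungated pairwise tests and on a change-score stand-in for the ANOVA; an omnibus reading gives less.

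A reader might infer that a false-positive claim is likely. The documents do not support that: it would need 0.05, three primary scales and free choice among tests all at once, and even then the chance is only about one half. Treating the analyses as 27 independent chances (75% at 0.05) would also be wrong, because the tests are strongly correlated. The change is still worth making because it is cheap and leaves one answer per contrast and primary outcome.

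**What to change.** 1. Name low-back NRS as the primary pain scale and list sciatica NRS as secondary.
2. Name one confirmatory test per outcome: the ANCOVA contrast at 12 months, adjusted for the baseline value of that outcome.
3. Test the three pairwise contrasts on RMDQ and low-back NRS, six tests in all, at the two-sided 0.01 already used for the sample size, and report 99% intervals. Family-wise error is then at most 6 × 0.01 = 6%, and about 5% in simulation.
4. Label the t-test/Mann-Whitney comparisons, the group-by-time ANOVA and the within-arm paired tests as supportive.
5. State that 51 completers per arm give about 89% power for RMDQ at 0.01.

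**Cost.** Wording only, with no extra patients; sciatica NRS loses primary status. If a strict 5% limit is wanted, the level becomes 0.05/6 = 0.0083. That needs 55 per arm for RMDQ at 90% power, or 55/0.85 = 64.7, so 65 with attrition; at 51 completers RMDQ power would be 87.5%.

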#### Secondary outcomes

**Pain coping strategies** The Coping Strategies Questionnaire (CSQ) assesses the frequency of several cognitive and behavioural strategies to cope with pain [39]. Patients must select in a Likert-type scale how often they use each strategy. It comprises seven subscales, six for cognitive strategies (ignoring pain, reinterpretation of pain, diverting attention, coping self-statements, catastrophizing and praying/hoping) and one for behavioural strategies (activity level). This questionnaire has been validated in the Spanish population and has shown good psychometric properties for evaluating patients with chronic musculoskeletal pain [40].

**Anxiety and depression** Levels of anxiety and depression will be assessed using the Hospital Anxiety and Depression Score (HADS) questionnaire. This questionnaire is widely used in clinical practice [41]. It is a fourteen-item scale where seven of the items are related to anxiety and the other seven to depression. The Spanish version has shown good internal consistency and external validity, as well as an adequate sensitivity to identify clinically significant depression [42].

**Fear-avoidance beliefs** The Fear-Avoidance Beliefs Questionnaire (FABQ) will be used to measure this domain. Is a scale composed of sixteen items developed to assess patients’ beliefs and attitudes about the causes and consequences of their low back pain [43]. Participants rate their agreement with each statement on a 7-point Likert scale (0 = completely disagree, 6 = completely agree). The FABQ consists of 2 subscales. The first sub-scale is the Physical Activity subscale (FABQpa), composed of seven items, which assesses the effects of physical activities on pain. The second subscale is the Work subscale (FABQw), composed of four items, which assesses the way that work activities can affect pain. The Spanish version has shown excellent psychometric properties [44].

**Catastrophizing** The Pain Catastrophizing Scale (PCS) tests the tendency to consider pain as a threat with exaggerated negative consequences in a patient [45]. It is a 13-item self-report scale, with each item evaluating the pain experience. For example: “I become afraid that the pain will get worse”. Participants assess the frequency at which these ideas appear on a Likert-type scale ranging from 0 to 4, with 0 being “not at all” and 4 “all the time”. The PCS yields a total score and three subscale scores examining rumination, magnification and helplessness. A high score on the total PCS score indicates a high level of catastrophizing. The Spanish version of PCS has demonstrated adequate psychometric properties [46].

**Quality of life** The SF-12 is the brief version of the 36-item Short Form Health Survey (SF-36). It contains items that measure each of the eight concepts included in the SF-36, namely physical functioning, role limitations due to physical health problems, bodily pain, general health, vitality (energy/fatigue), social functioning, role limitations due to emotional problems and mental health (psychological distress and psychological well-being). The SF-12 contains six-point scales in which patients evaluate the frequency and intensity of each statement over the past month [47,48].

#### Other measures

Demographic information will be collected on the following: age, gender, educational level, current marital status, physical activities (type and frequency) and work (according to the National Economical Activities Classification). Participants will be asked to choose between the following physical activity statuses: sedentary, sedentary with light ambulation, light or vigorous physical activity.

**Clinical data** Weight and height, pain duration (in months), pharmacological treatment history (NSAIDs, analgesics, anxiolytic, skeletal muscle relaxants and corticosteroids (specifying type, duration and dosage)), physical therapy (type and duration), imaging and other radiological tests, neurophysiological tests, as well as work status will all be recorded. These data will be gathered by interviews and from the participants’ clinical history.

Comorbidity will also be considered. Different factors like hypertension, arthrosis, diabetes, heart disease, chronic obstructive pulmonary disease (COPD) or smoking can affect the course of low back pain and its disability. Comorbidity will be assessed with the Charlson comorbidity index (CCI) [49]. The CCI evaluates 13 different comorbid conditions. Each condition is assigned a score depending on the risk of dying associated with each one. Scores are added to provide a total score to predict mortality. Psychiatric comorbidity will be evaluated with the Brief Symptom Inventory (BSI) [50] adapted by Ruipérez et al. [51].

Finally, all the different interventions that patients could receive besides the treatments offered in this study will be recorded using the interview with the patient and the clinical history as sources. Pharmacological treatment, physical therapy (in public or private services) and infiltrations will also be recorded.

**Satisfaction with the treatment** The Spanish adaptation of the Borkovec and Nau questionnaire [52] will be used. Participants have to respond using an 11-point scale (0 to 10) to give their opinion on the treatment received (for example, how logical the treatment was for them; if they are satisfied; if the treatment was useful; and if they would recommend the treatment to other people). Clinicians will also answer an adapted version of the questionnaire regarding satisfaction with the treatment program.

### Experimental conditions

There are three experimental conditions: control group, CBT group and CBT with ICT group. All participants, regardless of group assignment, will receive the same rehabilitation treatment (back school), which will be carried out by the same physiotherapist blinded to group assignment. CBT sessions in the experimental groups will be administered by a psychologist who does not belong to the staff of the healthcare centre where the trial will take place (students of the PhD program or Master's degree at Universitat Jaume I and University of Valencia, without special clinical training). The psychologists of the project research team will conduct the training of the psychologists who will apply the CBT program.

### Control group (Rehabilitation treatment and information)

Patients will receive the traditional rehabilitation treatment (back school). This treatment will consist of a 4-session group therapy every week, with each session lasting 45 minutes. The content of the first session will be educational (ergonomics, pain demystification) and the other three will include physical therapy focused on stabilisation training: lower extremity stretching; finding the neutral spine position; spine stabiliser activation (transversus abdominis and multifidus); abdominal, spinal extensor and lower extremity strengthening; and proprioceptive control (stabilisation kinesitherapy) [53,54].

### CBT group (traditional cognitive behavioural therapy) (CBT)

Patients will receive the same treatment in physical therapy as the control group, in addition to CBT. The aim of the CBT intervention is to produce changes in the beliefs and behaviours about physical activity and avoidance of activity. The treatment’s components are:

– Psychoeducation to counteract the misconceptions about low back pain and to highlight the relevance of maintaining an adequate level of activity.

– Cognitive restructuring techniques to modify misbelieves about low back pain and reduce catastrophizing.

– Behavioural therapy and activity pacing to decrease avoidance behaviours linked to pain and promote physical activity and meaningful activities.

– Training on self-management pain techniques (mindfulness and relaxation).

It is a 6-session group therapy, with one session per week. Each group will be composed of 6 to 8 participants. Each patient in this group will have to attend the assessment sessions and at least 4 out of 6 CBT sessions.

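### CBT is delivered in therapy groups of 6 to 8, but the sample size and every named test treat participants as independent, so CBT standard errors are too small and disability power is overstated

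*Protocol article*

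**What the plan says.** The section on the CBT group describes six weekly group sessions and fixes the group size: "Each group will be composed of 6 to 8 participants". The CBT + ICT section gives that arm the same interventions, with a web tool and text messages added for use at home. Participants are randomised individually. With 60 per arm, each CBT arm has about 8 to 10 therapy groups (60/8 = 7.5; 60/6 = 10).

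The Sample size section plans for "changes of 2 points in the pain intensity measured by the numerical rating scale (NRS) and of 3 points in the RMDS". It takes the variability from an earlier sample: "the mean disability according to the RMDS presented a standard deviation of 4, while the mean pain intensity displayed a standard deviation of 2". With "an alpha of 0.01 and a beta of 0.9 for two-tailed mean tests" it concludes that "the required sample size is 53 to detect changes in disability and 30 to detect changes in pain intensity", and then: "Considering an attrition of 15%, the sample will need 60 participants per condition". It mentions no ICC or design effect.

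The section Collection and data analysis names t-tests, Mann-Whitney tests, ANCOVA, ANOVA by group and time, and linear regressions. For the ANCOVA it says: "In all the tests, the independent variable will be the group, while the covariate variable will be the basal level of each dependent variable". There, group means trial arm. No model has a term for therapy group or therapist, and the limitations in the Discussion do not mention clustering.

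**The concern.** People who attend six sessions together share a leader, a group dynamic and a calendar period. Their outcomes are therefore likely to be positively correlated. When whole therapy groups belong to one arm, that correlation adds directly to the variance of the arm mean. An analysis by participant ignores it, so confidence intervals are too narrow and p-values too small. A particularly good or poor group can then pass for a treatment effect.

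The direction of the error is known. It reaches both comparisons of a CBT arm with control and also CBT+ICT versus CBT, the contrast that shows whether the technology adds anything. The Experimental conditions section says that sessions are led by students without special clinical training, so differences between leaders are plausible.

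**Working it through.** **Inputs from the document (Sample size; CBT group).** Disability: difference 3, SD 4. Pain: difference 2, SD 2. Two-sided alpha 0.01. The stated beta of 0.9 is read as power 0.90. 60 recruited per arm, 15% attrition, therapy groups of 6 to 8.

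**Assumptions.** The ICC is not given; I use 0.01, 0.05 and 0.10. Evaluable n per arm is 60 × 0.85 = 51. Evaluable group size is m = 6, since 7 × 0.85 = 5.95. The raw SD is used, with no gain from baseline adjustment.

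**Reproducing the plan.** n per arm = 2 × [SD × (2.576 + 1.282) / difference]².
- Disability: 52.9, rounded up to 53.
- Pain: 29.8, rounded up to 30.

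Both stated figures come out exactly under independence, so no allowance for clustering is hidden in them.

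**Adding the therapy groups.** The design effect is DE = 1 + (m − 1) × ICC.
- Both arms clustered (CBT+ICT versus CBT): SE = SD × √(2 × DE / n), and the variance ratio against the naive analysis is V = DE.
- Only the CBT arm clustered (CBT versus control): SE = SD × √((1 + DE) / n), and V = (1 + DE) / 2.
- Power = Φ(difference / SE − 2.576).
- True size of the naive test = 2 × [1 − Φ(z / √V)], with z = 2.576 for nominal 0.01.

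Worked case, disability, both arms, ICC 0.05: DE = 1 + 5 × 0.05 = 1.25. SE = 4 × √(2.5 / 51) = 0.886. Power = Φ(3 / 0.886 − 2.576) = Φ(0.81) = 0.79. Size = 2 × [1 − Φ(2.576 / 1.118)] = 0.021.

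Results for disability, m = 6, 51 evaluable per arm:

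| ICC | DE | CBT+ICT vs CBT: power | size at 0.01 | CBT vs control: power | size at 0.01 |
|---|---|---|---|---|---|
| 0 | 1.00 | 0.89 | 0.010 | 0.89 | 0.010 |
| 0.01 | 1.05 | 0.87 | 0.012 | 0.88 | 0.011 |
| 0.05 | 1.25 | 0.79 | 0.021 | 0.84 | 0.015 |
| 0.10 | 1.50 | 0.70 | 0.035 | 0.79 | 0.021 |

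The analysis section states no test level. At nominal 0.05 the true size over the same ICC range would be 0.056 to 0.110 with both arms clustered, and 0.053 to 0.080 with one.

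**Sample size for 90% disability power** (evaluable per arm, m = 6, ICC 0.01 / 0.05 / 0.10): 55 / 60 / 67 with one arm clustered and 56 / 67 / 80 with both.

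**Pain, both arms clustered, m = 6.** Power is 0.99, 0.97 and 0.94 at the three ICCs. Even with m = 8 and ICC 0.10 it is 0.90. The size inflation is the same as for disability, because it depends only on V.

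**Limits of the calculation.** It uses normal quantiles. With only about 8 to 10 therapy groups per arm these are somewhat optimistic.

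**The case against.** **The size rests on an unknown ICC.** This stands. At 0.01 the effect is negligible (power 0.87 against 0.89, size 0.012 against 0.010). It becomes material from about 0.05. At a test level of 0.01, even the upper figure of 0.035 stays below 0.05.

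**Baseline adjustment recovers power.** This stands in part. The planned ANCOVA reduces the residual SD to 4 × √(1 − r²), but the document gives no baseline-to-12-month correlation r. If r is assumed to be 0.4 to 0.6, disability power for CBT+ICT versus CBT (m = 6) is 0.87 to 0.95 at ICC 0.05 and 0.79 to 0.90 at ICC 0.10. The table is therefore not the power of the planned ANCOVA. It is on the same footing as the plan's own calculation, which also takes no credit for baseline. Adjustment does not cure the type I error.

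**Arm-specific groups and therapists are not stated.** This stands as a condition. Separate therapy groups are the natural reading, but no sentence says so. If groups mixed the two CBT arms, therapy group would be crossed with arm, and ignoring it would not inflate CBT+ICT versus CBT. A reader might also infer that a good or poor therapist biases that contrast. The document does not allocate therapists to arms, and if the same people serve both, their effects largely cancel.

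**Controls are also treated in groups.** This stands. Back school is group therapy in all three arms, and neither its group size nor whether arms mix is described. The figures for CBT versus control hold only if it adds no arm-specific clustering.

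**This can be left to the analysis plan.** This does not stand for the main point. The article itself fixes a sample size that assumes independence and names the participant-level tests.

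**Conclusion.** The point holds. Both experimental arms receive group-delivered CBT, while the sizing and every named test assume independent participants. With any positive ICC, standard errors for CBT contrasts are too small and the 90% disability power is overstated.

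The size is conditional on the assumptions listed in the working. Over ICC 0.01 to 0.10 it runs from negligible to a loss of 19 percentage points of disability power (0.89 to 0.70) and a true size of 0.035 at nominal 0.01. Those upper figures are for CBT+ICT versus CBT with arm-specific groups. CBT versus control is affected less.

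Two stronger readings are tempting and are not supported. One is that the trial is underpowered in general: pain keeps at least 90% power throughout, so the power loss concerns disability only, although type I error inflation affects both primary outcomes. The other is that CBT+ICT versus CBT is certainly the contrast hit hardest, which depends on groups being arm-specific, and the document does not say so.

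**What to change.** 1. State whether therapy groups and back-school groups are arm-specific or mixed, and whether the same psychologists serve both CBT arms.
2. Record therapy-group, therapist and back-school-group identifiers for every participant at delivery; they may be hard to recover later.
3. Analyse both primary outcomes with a baseline-adjusted partially nested mixed model. Include a random therapy-group effect in the two CBT arms and use small-sample degrees of freedom (Kenward-Roger or Satterthwaite). Treat controls as singletons only if back-school groups mix arms or show no clustering. Treat therapist as crossed with arm if therapists serve both CBT arms.
4. Restate disability power over an assumed ICC range, saying what correlation with baseline is assumed, if any.

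The cost is three identifier fields and revised analysis and sample-size wording; no treatment changes. The downside is wider intervals and a less favourable power statement. If the sponsor wants to keep 90% disability power at a moderate ICC without relying on baseline adjustment, more participants would be needed, as the working shows.
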